## Methods

### Study design

This is a randomized, double-blinded, sham-controlled and single-center clinical study (Registry: Chinese Clinical Trial Registry; Registration number: ChiCTR2600125453). Patient with PSA will be recruited and will be randomized 1:1 into two groups: the sham and real stimulation group. Patient in the real stimulation group will receive rTMS targeting the right cerebellum, as well as conventional language rehabilitation training. While the sham stimulation will be implemented in the sham group. Language and cognitive function evaluation and neuroimaging data will be collected before rTMS treatment (T0) and at 2 weeks (T1), 3 months (T2), 6 months (T3), and 1 year (T4) after treatment (Please see more details in Fig 1 and Fig 2). The trial protocol conforms to the Standard Protocol Items: Recommendations for Interventional Trials (SPIRIT) Checklist (S1 Checklist) [40]. All participants have provided signed informed consent (S2 File). The study will adhere to the guidelines set forth in the Declaration of Helsinki.

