### Outcome measurement

Outcome measures will be assessed across five time points: prior to rTMS treatment (T0), and at 2 weeks (T1), 3 months (T2), 6 months (T3), and 1 year (T4) post-treatment. The primary outcome is the evaluation of language function. Neuroimaging data, along with evaluations of non-linguistic cognitive functions, will serve as secondary outcome measures (Table 1).

**Table 1 pone.0354837.t001:** Outcome measures.

Outcome measures
**Primary outcome measures** ● WAB for determining the presence of aphasia and assessing language dysfunction recovery and deterioration.
**Secondary outcome measures** ● Imaging data for evaluating the structural, function and perfusion alterations in brain area. ● LOTCA for assessing nonverbal cognitive function.
**Safety outcome** ● Incidence of adverse events. ● VAS for assessing headache symptoms. ● FSAS for assessing fatigue symptoms.

Abbreviation: WAB: West Aphasia Battery; LOTCA: The Loewenstein Occupational Therapy Cognitive Assessment; VAS: Visual Analog Scale; FSAS: Fatigue Self-Assessment Scale.

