#### Primary outcome measurement.

The West Aphasia Battery (WAB) will be utilized to assess and monitor the improvement and deterioration of aphasia [42]. The assessment involves six language functions, which include spontaneous speech, auditory verbal comprehension, repetition, naming and word finding, reading, and writing. In the evaluation of aphasia, the AQ score is calculated to determine the severity of the condition. A higher AQ score indicates a milder form of aphasia and better language capabilities. The formula for calculating the AQ score is as follows: AQ = 2 × (spontaneous speech + auditory comprehension/20 + repetition/10 + naming/10). The total score is 100 points; higher scores suggest milder aphasia and improved language skills. AQ < 93.8 signifies aphasia.

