### Statistical analysis

#### Behavior data analysis.

SPSS 26.0 statistical software will be used to analyze behavior data (the performance of scale assessment which mentioned above). We will use the Intention-to-treat analysis in this study. Shapiro-Wilk test will be used to verify whether the data are normally distributed. For normally distributed measures, t-test and repeated-measures analysis of variances will be used to compare the behavior functions between the same group before and after treatment and between the real and sham rTMS group in the same phase. For non-normally distributed measures, the Mann-Whitney U Test and Kruskal-Wallis H test will be used for comparison across the conditions. P-value < 0.05 is considered significant (two-tailed).

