#### Imaging data analysis.

MRI preprocessing and statistical analyses of all images will be implemented on MATLAB2021b (https://ww2.mathworks.cn) using statistical parametric mapping software (SPM12, https://www.fil.ion.ucl.ac.uk/spm/software/spm12/).

The processed data from DTI, rs-fMRI, and ASL will be employed to evaluate cerebellar stimulation’s effect on aphasia recovery in terms of structure, function, and perfusion. For the DTI data, variations in the cerebral-cerebellar loop’s structure will be identified between different groups and pre-/post treatment using Tract-Based Spatial Statistics (TBSS) analysis. With rs-fMRI, the analysis of amplitude of low-frequency fluctuations (ALFF), regional homogeneity (ReHo), and functional connectivity density (FCD) will be completed to assess the local and global functional connectivity inside the language networks. Using ASL sequences, the cerebral perfusion for every participant will be calculated, targeting the perfusion alteration, particularly the lesion area. One-way ANOVA will be performed to compare the imaging parameters among the groups (pre-vs. post-treatment, real vs. sham treatment). A linear regression analysis will be applied to establish the relationship between behavioral performance and the parameters. Any differences among these conditions are regarded as significant when the P-value is < 0.05 at the voxel level, with an FDR cluster-corrected P-value < 0.05 (two-tailed).

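### For non-normal behavior scores the plan names only independent-sample rank tests, although it also plans before/after comparisons in the same patients

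*Protocol article*

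**What the plan says.** The Behavior data analysis section of the protocol article sets two kinds of comparison for the scale scores. It will "compare the behavior functions between the same group before and after treatment and between the real and sham rTMS group in the same phase". For normally distributed measures it names the t-test and repeated-measures ANOVA. For the rest it says: "For non-normally distributed measures, the Mann-Whitney U Test and Kruskal-Wallis H test will be used for comparison across the conditions". No other rank method appears in the section.

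Two design facts bear on this. Under Study design, patients "will be randomized 1:1 into two groups: the sham and real stimulation group", so there are only two independent groups. Under Outcome measurement, the same patients are seen repeatedly: "Outcome measures will be assessed across five time points: prior to rTMS treatment (T0), and at 2 weeks (T1), 3 months (T2), 6 months (T3"), with a fifth visit at 1 year (T4).

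The next section, Imaging data analysis, also counts before/after among the conditions. Its one-way ANOVA is to "compare the imaging parameters among the groups (pre-vs. post-treatment, real vs. sham treatment").

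**The concern.** Mann-Whitney U and Kruskal-Wallis H derive their null distributions from independent samples. Scores from one patient at two visits are not independent. Both tests leave the stable differences between patients in the error term, whereas a paired test removes them by comparing each patient with himself or herself.

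The sentence that names the two tests follows directly on one that includes same-group before/after comparisons, and nothing limits the tests to the between-arm part. Kruskal-Wallis points the same way. It is a test for three or more independent groups, and the trial has two. Its only evident use is across the five visits, which hold the same patients.

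The within-arm results are at stake. Real improvement in a non-normal scale could be reported as not significant because the test does not suit the data.

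**Working it through.** **1. The plan's own figure.** Sample size gives d = 0.86, two-sided α = 0.05, power 90% and 1:1 allocation. The two-sample t calculation gives 29.41, rounded up to 30 per group, with power 0.906 at 30. Then 60 × 1.10 = 66. The stated figures reproduce, and they concern the between-arm comparison, so this point does not touch them.

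**2. Inputs for the check.**
- From the protocol: 30 patients per arm before dropout allowance, five visits, two-sided 0.05.
- Assumed, because the protocol gives none: between-visit correlation r from 0.3 to 0.9, equal for all pairs of visits, and an improvement of 0.4 SD reached linearly at T4.

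**3. Approximate null level.** With common SD σ and n patients, an independent-sample test takes the standard error of a T0-to-T4 difference as σ√(2/n). The actual standard error is σ√(2(1 − r)/n). The true two-sided level is therefore about 2[1 − Φ(1.96/√(1 − r))].
- r = 0.3: 1.96/0.837 = 2.34, level about 1.9%
- r = 0.5: 1.96/0.707 = 2.77, level about 0.6%
- r = 0.9: 1.96/0.316 = 6.20, level effectively 0

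**4. Approximate power for 0.4 SD.** The assumed standard error is √(2/30) = 0.258, so the test needs a difference of 1.96 × 0.258 = 0.506 SD.
- r = 0.3: actual standard error 0.258 × 0.837 = 0.216. Power if treated as independent: 1 − Φ((0.506 − 0.4)/0.216) = 1 − Φ(0.49), about 31%. Paired: Φ(0.4/0.216 − 1.96) = Φ(−0.11), about 46%.
- r = 0.9: actual standard error 0.258 × 0.316 = 0.082. Treated as independent: 1 − Φ(0.106/0.082) = 1 − Φ(1.29), about 10%. Paired: Φ(0.4/0.082 − 1.96) = Φ(2.92), above 99%.

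**5. Simulation of the rank tests themselves**, on the inputs in step 2 (first value r = 0.3, last value r = 0.9):

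| Within-arm comparison | True null level | Power, 0.4 SD |
|---|---|---|
| Mann-Whitney, T0 vs T4 | about 2% to 0% | about 30% to 13% |
| Wilcoxon signed-rank, T0 vs T4 | about 5% | 41% to 99% |
| Kruskal-Wallis, five visits | about 1% to 0% | 14% to 1% |
| Friedman, five visits | about 5% | 26% to 98% |

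**6. Skewed data.** A separate simulation used log-normal scores, 30 patients and 4,000 runs, with a shift of 0.5 SD on the log scale between two visits:

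| r | Level, Mann-Whitney | Level, Kruskal-Wallis | Power, Mann-Whitney | Power, signed-rank |
|---|---|---|---|---|
| 0 | 5.3% | 5.3% | 46% | 42% |
| 0.3 | 2.4% | 1.3% | 44% | 53% |
| 0.5 | 0.75% | 0.18% | 45% | 66% |
| 0.7 | 0.05% | 0% | 45% | 86% |
| 0.9 | 0% | 0% | 44% | 100% |

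The paired tests stayed between 4.5% and 5.7% throughout. The named tests hold their level only at r = 0, which is not credible for repeated scores in one patient.

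**7. Between arms.** Mann-Whitney on two independent groups of 30 rejected in about 4.5% of null runs, as it should.

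**The case against.** The strongest reply is that the trial's question is real versus sham, and there the named test is right. Mann-Whitney is valid for the two arms at one visit. It is equally valid for the change in AQ from baseline, and the Abstract defines the primary outcome as change to the final follow-up. With 30 per arm and d = 0.86, a simulation gave it a null level of 5.2% and power of 89%, close to the planned 90%. Within-arm comparisons do not test efficacy, and the error in them goes in the safe direction. All of this stands, and it limits the point.

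It does not remove it. If the two tests are meant only for real versus sham, the before/after comparison that the section promises has no test for non-normal scores, and Kruskal-Wallis has no job.

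A reader might infer more than the text supports:
- *Shared recovery would be declared a treatment effect.* This would need one Kruskal-Wallis over all ten arm-by-visit cells. The protocol describes no such analysis; it names the two comparisons separately. Rejecting equality of all cells when patients do recover would also be a correct rejection that is then misread, not a type I error.
- *The primary outcome will probably fall into this branch because AQ is capped at 100.* Eligibility sets AQ below 93.8 with no lower bound, NIHSS ≤ 3 is not an AQ threshold, and no AQ distribution is given. A ceiling is possible but not shown.
- *The method can switch from visit to visit.* The text chooses the branch by measure, not by visit.

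**Conclusion.** The point holds for within-patient comparisons of non-normal measures. The named tests belong to the wrong family, and this is a method that the article states, not a detail left to an analysis plan.

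The direction is firm: at every positive correlation tried, the true level falls below 5%. The size of the power loss depends on r, on the size of the improvement and on its time course, none of which the protocol gives, so only the range should be quoted. The loss is modest at r = 0.3 (about 30% against 41% for two visits) and severe at r = 0.9 (about 13% against 99%).

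The consequence is missed change, not false claims of benefit. The documents do not support the conclusion that the treatment comparison or the sample size is unsound.

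**What to change.** In Behavior data analysis, replace the sentence on non-normal measures so that each comparison has its own test:
- Real versus sham: Mann-Whitney U only, at the same visit or on the change in AQ from baseline.
- Within one arm: Wilcoxon signed-rank for two visits, Friedman for all five.
- Remove Kruskal-Wallis.

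The cost is analysis wording only. Sample size, visits and data collection stay as they are. Trial status puts the end of recruitment at December 31, 2028, so the change can be made well before analysis.

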**Methods:**

Our study will recruit sixty-six PSA patients, who will be randomly divided into either a real or a sham rTMS group with equal distribution. The real rTMS group (n  =  33) will receive rTMS treatment over the right cerebellar hemisphere along with speech-language therapy (SLT), while the sham group (n  =  33) will receive sham stimulation and SLT. We will assess the outcomes at five intervals: before rTMS treatment, 2, 12, and 24 weeks, and 1-year post-treatment. The primary outcome in this research is the change in performance of the West Aphasia Battery from baseline to the final follow-up. Secondary outcomes include alterations in the structure, function, and perfusion neuroimaging data, as well as changes in non-verbal cognitive functions, measured using the Loewenstein Occupational Therapy Cognitive Assessment over time and between the groups. Any adverse event related to rTMS therapy will also be recorded. The results of this trial will provide insights into whether cerebellar rTMS stimulation (1) improves language function recovery in subacute phase PSA patients; (2) strengthens the functional connection of the cerebro-cerebellar network, and (3) enhances aphasia treatment outcomes by improving non-linguistic cognitive functions. We commenced patient recruitment for this trial in June 2026, and it is currently in progress.

**Registration** This project was prospectively registered at the Chinese Clinical Trial Registry (ChiCTR2600125453).

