The majority of prior research, however, has focused on chronic stroke phase aphasia patients whose functional brain structures have already undergone irreversible alterations [4,33,34]. This could potentially explain the observed lack of significant effects of cerebellar NIBS on language recovery [22,35]. Recent guidelines indicate the safe and tolerable application of NIBS even in the sub-acute phase, with no severe adverse effects reported [36–39]. The current study protocol proposes to stimulate the right cerebellum with repetitive transcranial magnetic stimulation (rTMS) in order to enhance SLT for PSA patients in the sub-acute phase. The study’s primary objective is to assess the short- and long-term efficacy of cerebellar rTMS for aphasia recovery in these patients under a randomized, sham-controlled design. The secondary purpose is to examine alterations in functional connectivity between the cerebellum and language-related cortical regions pre- and post-treatment and elucidate the neural restructuring mechanism. Moreover, from a neuropsychological perspective, the study will investigate whether cerebellar stimulation can improve language symptoms through enhancing non-linguistic cognitive functions.

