### Sample size

The sample size was estimated using G*power of 3.1.9.6 (www.gpower.hhu.de) [43–44], with the following parameters: effect size (*d*) = 0.86, α = 0.05 (two tails), power (1–β) = 90%, and allocation ratio n2/n1 = 1. The effect size was determined based on the result of our pilot study. The sample size in the current study should be 60 (30 in each group) after calculation. Considering a 10% dropout rate, a total of 66 patients are aimed to be recruited finally.

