### Trial innovation

The proposed study protocol, featuring a rigorous randomized, parallel, controlled trial design, adheres to the methodological prerequisites of full concealment, randomization, and sham control. This approach is advantageous as it reduces bias and provides robust evidence to evaluate the effectiveness of cerebellar rTMS, thus, drawing a reliable conclusion [53].

Further, the choice of the sub-acute stroke phase as the intervention period is strategic. This period is in a neuroplasticity window making the brain particularly receptive to modulating intervention early in the recovery course [54]. Existing imaging studies on PSA generally agree that a brain activation shift, induced by tasks, transpires within the initial post-stroke weeks, followed by a normalization of activity patterns over several months [55–56]. Hence, we hypothesize that delivering the treatment during the subacute stroke phase could yield more significant effects than in the chronic phase. The effectiveness of the intervention will be assessed at various time points: pre-intervention, the second week’s end, the third and sixth months, and one-year post-intervention. This will enable a comparison of efficacy across different periods and the identification of the earliest effective treatment time.

Unlike many preceding studies that predominantly applied transcranial direct current stimulation (tDCS), this research will employ rTMS treatment. Compared to tDCS, rTMS creates resilient, enduring activation alterations in noticeably shorter timeframes [57]. Moreover, we will utilize a figure-of-8 coil on the cerebellum, proven to be a flat coil model with improved trial tolerances that can effectively stimulate the cerebellar cortex’s superficial layers [58].

Another unique point is that the current study will investigate the profound neuropsychological and neural network mechanisms influencing the impact of cerebellar rTMS on aphasia – a subject area relatively unexplored in previous research [20,22,59]. A multi-modal neuroimaging technique will be used to gauge modifications in the supratentorial areas’ structure, function, and perfusion, particularly the lesion part after treatment. This will also give insights into the relationship between these changes and language, along with non-verbal cognitive functions recovery.

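### The body of the protocol does not hold to the Abstract's single primary contrast: it names no primary visit or decisive test and compares the arms at every phase at 0.05

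*Protocol article*

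**What the plan says.** All references are to the protocol article.

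- **Abstract, Methods:** "The primary outcome in this research is the change in performance of the West Aphasia Battery from baseline to the final follow-up". This is one contrast at one visit, although the score within the WAB is not named.
- **Outcome measurement:** "The primary outcome is the evaluation of language function". No time point is attached. Table 1 lists the WAB as the primary measure, also without a visit. A separate sentence schedules all outcome measures at T0 and at four later visits, T1 to T4.
- **Primary outcome measurement:** describes six language functions and defines the aphasia quotient (AQ) as the severity score, but does not say which score is primary.
- **Introduction:** the primary objective is to "assess the short- and long-term efficacy of cerebellar rTMS for aphasia recovery".
- **Sample size:** d = 0.86 from a pilot study, "α = 0.05 (two tails", 90% power, equal allocation; 30 per arm, 66 in total with dropout. The score and visit behind d are not stated.
- **Behavior data analysis:** t-tests and repeated-measures ANOVA, or Mann-Whitney and Kruskal-Wallis tests if data are not normal. They serve for before-after comparisons within each arm and for real versus sham in each phase. The rule is "P-value < 0.05 is considered significant (two-tailed".
- **Trial innovation (Discussion):** the visit schedule is expected to allow "the identification of the earliest effective treatment time".

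**The concern.** A reader of the Abstract and the sample size expects one confirmatory test. A reader of the Methods finds up to four real-versus-sham comparisons of the same outcome, each judged at 0.05, and nothing saying which one decides the trial. The objective and the Discussion both give a reason to look at every visit.

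At stake is what may be reported as the primary result. If the one-year difference is not significant but an earlier one is, the body does not prevent the earlier one from being presented as the primary finding. The risk is practical, because the limitations section concedes unpredictable dropout over the year, so T4 is the visit most exposed to missing data.

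The timing aim has its own weakness. The first visit with P < 0.05 depends on the variability and the number of patients at each visit as well as on the effect, so it does not show when an effect begins.

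**Working it through.** **1. The plan's own figure.** Inputs from the Sample size section: d = 0.86, two-sided alpha 0.05, power 90%, ratio 1.

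Two-sample t-test with n per arm: noncentrality = d × √(n/2), degrees of freedom = 2n − 2.
- n = 30: noncentrality = 0.86 × √15 = 3.33, df = 58, power = 90.6%.
- n = 29: power = 89.6%, below target.

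So 30 per arm (60) reproduces, and 60 × 1.10 = 66. The calculation covers one comparison with the whole 5% spent on it.

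**2. One primary test.** For the Abstract's contrast, tested once at 0.05, the false-positive rate is 5%.

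**3. Any of four visits counted as efficacy.** This is a conditional scenario, not a rule in the document.
- Independent tests: 1 − (1 − 0.05)⁴ = 1 − 0.8145 = 18.5%.
- Correlated tests: four two-sample t-tests, 30 per arm, no true difference at any visit, equal correlation r between visits, 100,000 simulated trials per setting. The document gives no r, so every value is an assumption.

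| Assumed r | Chance of at least one P < 0.05 |
|---|---|
| 0 (formula) | 18.5% |
| 0.5 | 15.5% |
| 0.7 | 13.2% |
| 0.8 | 11.6% |
| 0.9 | 9.3% |
| 0.95 | 8.0% |

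If correlation instead decays with the number of visits apart, the result is 14.5% (0.7 between neighbours) and 10.1% (0.9). The rate stays above 5% throughout.

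**4. What each resolution costs.**
- One primary contrast: alpha 0.05, 30 per arm, power 90.6%. Nothing changes.
- Four co-equal tests with Bonferroni: 0.05/4 = 0.0125 each. At 30 per arm, power per test falls to 77.1%. Restoring 90% needs 41 per arm, that is 82 evaluable and 82/0.9 = 91.1, so 92 enrolled.

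The stated sample size therefore fits only the first option.

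**The case against.** The strongest reply is that the Abstract names one contrast and the sample size funds one test, so the trial's error rate is 5% and the Methods are merely less specific. Measuring at five visits is compatible with a primary analysis at T4. Test order and multiplicity adjustment are commonly left to a statistical analysis plan, which is not shown here. Repeated-measures ANOVA is listed and could serve as one overall test.

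Much of this stands, and it rules out several stronger readings that a reader might infer:

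- **That the trial's false-positive rate does exceed 5%.** It does so only if success at any visit counts. The document neither states that rule nor excludes it.
- **That six WAB functions at four visits make 24 primary tests.** No section plans such tests; the functions are described as components of the battery.
- **That the plan will pick the earliest effective time by significance at each visit.** The aim stands in the Discussion, says only what the schedule will allow, and is not tied to particular tests.
- **That the lack of an adjustment is itself the error.** It could lie in an analysis plan that is not shown.

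The reply does not remove the mismatch. An unseen analysis plan would not make the Outcome measurement section agree with the Abstract. The ANOVA stands beside the t-test without being made decisive, and an overall group or group-by-time test would not be the Abstract's T0-to-T4 contrast. If the data are not normal, the two tests offered are for independent samples, so neither gives an overall longitudinal comparison.

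**Conclusion.** The point holds as an inconsistency within the document. The Abstract and the sample size support one primary contrast. The Outcome measurement section, Table 1, the primary objective and the Behavior data analysis section do not hold to it and leave the deciding visit, score and test open.

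The size is conditional. It is 5% if the Abstract's contrast is tested once, and about 8% to 18.5% if any of T1 to T4 were accepted as showing efficacy. The second range rests on assumed correlations from 0.95 to 0 and on all four visits being tested at 0.05 with 30 patients per arm. It describes what the loose wording would permit; it is not an error rate that the plan commits itself to. The mismatch should be corrected before any outcome comparison by arm.

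**What to change.** 1. In Outcome measurement, Table 1 and Behavior data analysis, state that the between-arm difference in WAB change from T0 to T4, on one named score, is the only primary test, at two-sided 0.05. AQ is the summary score that the document defines; confirm that it is the measure behind d = 0.86 before naming it.
2. Say which of the listed methods delivers that test.
3. Label the arm comparisons at T1 to T3, the within-group comparisons and the WAB subscores as secondary or supportive, and report the arm comparisons as differences with confidence intervals.
4. Word the primary objective in the Introduction to match, with short-term efficacy as a secondary question.
5. Reword the earliest-effective-time aim in the Discussion as descriptive: arm differences with intervals at each visit.

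**Cost:** wording only. The 60 evaluable and 66 enrolled patients and the 90% power stand. The small downside is that results at T1 to T3 cannot be claimed as confirmatory.

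**One dependency:** the Trial status section ends recruitment on December 31, 2028 and data collection on June 1, 2029, five months later. Late recruits could not reach a one-year visit in that time, so these dates must be reconciled with T4 when it is fixed as the primary visit.
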